### Microrandomization Procedure

Each time a participant completes an EMA, responses will be assessed for intervention eligibility (Figure 1). If a participant is eligible for an EMI at that point in time, they will be randomized to one of the following two conditions: (1) specific strategies with facilitated action- and coping planning or (2) control group (strategy groups—strategy group level names only). Randomization to the 2 conditions occurs in real time within the app algorithm; at the time, the participant becomes eligible for the EMI and occurs on a 50:50 split between control and intervention. The microrandomization procedure used by *Gambling Habit Hacker* uses a fully automated randomization process, whereby a random number generator is embedded in the app. This guarantees that the administration of treatments and assessment of outcomes are fully blinded.

**Figure 1 figure1:**
[figure not shown]
Microrandomized trial design of *Gambling Habit Hacker*. AP: action planning; CP: coping planning; EMA: ecological momentary assessment; EMI: ecological momentary intervention.

### Intervention Options

#### Overview

The *Gambling Habit Hacker* app is part of a suite of interventions for addictive behaviors that delivers implementation support based on lived experience, along with goal setting, action planning, and coping planning [39,58,67]. In this study, *Gambling Habit Hacker* is delivered as a JITAI that delivers in-the-moment support for adhering to the gambling expenditure limits. The overarching set of principles guiding the *Gambling Habit Hacker* app is the HAPA [32] and self-determination theory [29]. HAPA guided the selection of BCTs: goal setting, action planning, coping planning, and self-monitoring as the mechanism for bridging the gap between intention and behavior. Self-determination theory guided the delivery of BCTs, whereby goal setting and planning were personalized to support individual autonomy and the development of competence [29,35]. In-app communication was nonjudgmental and respectful and aimed to support relatedness through the inclusion of lived experience information and quotes. In accordance with self-determination theory, participants can select any gambling expenditure limit, including reduction or abstinence [29].

#### Intervention Condition—Strategy Groups, Action Planning, and Coping Planning

Gamblers use a wide range of cognitive and behavioral strategies to limit or reduce their gambling behavior [15,17,18,20,23,26,30,68]. To support participants in selecting and implementing the right strategy at the right time, we developed a comprehensive list of strategy options. Each option contains a strategy name such as *social support* and implementation guidance such as *talking to someone about gambling*. Each strategy was categorized into a higher order group, which is referred to as a strategy group (n=25). Each strategy group contains between 4 and 6 strategies, each with detailed implementation guidance (120 strategies in total). For reporting and comparison with the broader literature, strategy groups were organized into 10 higher order BCT categories [14]. As indicated in Table 2, these were avoidance, rewards, substitution activities and social support, and categories of BCTs identified in the gambling literature [15], including maintaining momentum, staying in control while gambling, urge management, financial management, and managing emotions.

**Table 2 table2:** Individual strategies for adhering to gambling expenditure limits organized by behavior change technique (BCT) category and strategy group.

BCT category (n=10) and strategy group (n=25)			Individual strategies (n=120)
**Avoidance**			
	Stay away from venues		Ban yourself; go away now; block online venue; deal with social pressure.
**Financial management**			
	Keep to budget		Calculate cash allowance; get a debit card without cash access; block access to online banking; cancel or destroy credit cards; ensure you cannot draw money from assets; keep wages safe.
	Reduce cash in hand		Pay bills; buy essentials; set up savings account.
	Limit cash		Set a cash limit today; leave cards at home; change personal identification numbers; give cards to a family member; use prepaid cards; reduce automated teller machine limits.
**Maintaining momentum**			
	Build momentum		Know reasons for change; take it a day at a time; take it slow and steady; pause and celebrate.
	Strengthen goal		Keep your plan number 1; slow down the emotional roller coaster; let go of guilt and shame; get inspiration.
	Know reason for change		Identify gambling cons; change pros; know your rock bottom; identify harm; stop chasing losses; accept loss of control.
	Build commitment		Build confidence; build willpower; increase accountability; focus on today.
**Managing emotions**			
	Deal with emotions		Deal with boredom; deal with frustration; deal with pain; deal with anger; deal with loneliness; deal with happiness.
**Rewards**			
	Impose rewards and consequences		Accept a reward; give yourself a reward; create a future reward; set up a penalty system; give yourself a red card.
	Grab a treat		Feel good treat; get creative; connect with someone; achieve something; do something fun.
**Substitution activities**			
	Do something else		Get busy; get moving; connection; get a positive addiction; feel good.
	Swap gambling		Play low-cost games; play no cost pokies; play no cost casino games; get adrenaline in a different way; play other games.
**Social support**			
	Talk to someone		Talk it over; admit or confess; be accountable; get advice; find someone to support your goals.
	Seek professional support		Talk to a gambling counselor; talk to a counselor about mental health; talk to a financial counselor; go to a support group; go to a 12-step group; access online support.
**Staying in control while gambling**			
	Prepokies prep		Set your loss limit; set your time limit; leave cash and cards at home; leave cash and cards in the car; give cash and cards to a friend.
	Control cash in venue		Avoid automated teller machines; do not borrow money; keep winnings.
	Slow down the bets		Change machines often; take breaks; keep the same bet size; take time between spins; avoid chasing losses.
	Know when to walk away		Walk away when limits are reached; walk away when you hit your time limit even if it is fun; walk away when it is no longer fun; walk away from social pressure.
	Increase self-control in venue		Do not get comfortable; view gambling as entertainment; address thoughts of abandoning limits; avoid stimulants.
**Stress management**			
	Reduce stress		Sleep; take a walk; cut stimulants; relax; self-massage.
	Support good health		Eat healthy; cut alcohol; check your mental health; practice mindfulness; exercise.
**Urge management**			
	Control gambling urges		Stay away from a venue; reduce mental tension; walk out of a venue; remove access to cash; deal with payday; do something else; learn to say no.
	Reduce gambling thoughts		Deal with advertising; address thoughts of wining; address thoughts of gambling; deal with permission giving.
	Know tricks pokies play		Let go of lucky charms; remember pokies are based completely on chance; notice losses disguised as wins; remember no skill is needed.

Even though gamblers use a wide range of strategies, studies indicate that up to 80% of gamblers fail to adhere to their gambling limits [25]. Forming specific plans about how, when, and where to act has been shown to increase adherence to gambling limits in gambling venues [39]. The action planning component prompts participants to develop personally tailored action plans that respond to immediate threats to adhering to gambling limits. Participants allocated to the intervention condition received a list of tailored strategy groups (6-16 groups) based on the results of their EMA. Participants can select a strategy group, and the app then provides a list of all relevant individual strategies from which they can select. Upon selection, the app provides a detailed description of methods for implementation (drawn from lived experience research; see the *Consumer Participation* section [15]) and offers strategy-specific prompts for the personalization of the strategy. As an illustration of this process, if the participant were to select *Talk to someone* from the list of strategy groups, they would then be presented with a list of five individual strategies: Talk it over, Admit or confess, Be accountable, Get advice, and Someone to support your goals. If the participant then selected the strategy *Be accountable*, the app will provide the following information: *how to identify someone that will hold you accountable for your plan, different ways to involve others for accountability, how having someone for accountability can make you feel, and what can get in the way of your plans.* The app further prompts the participant to think of specific details, such as the name of the person they will be accountable to; why this person is a good option; and whether they will text, call, chat, or email that person. Once participants are provided with all the information and prompted to consider specific details, they are asked to record their action plan. The app produces the following prompt: *If this strategy sounds good to you, then take action. Write your plan here on how you will* (name of the strategy). *Include in your plan something you can do right now. Be specific about what you will do and how you will do it.* The prompt is followed by an open text field for the participant to detail their personalized, detailed action plan.

Action planning can bridge intention and behavior, but it does not directly address barriers that can get in the way of even the most robust plans. The coping planning component involves the development of a personally tailored coping plan in response to a proximal implementation barrier [69]. Action planning and coping planning are developed simultaneously, based on a series of prompts in the app. Participants are prompted to identify the main barriers to their action plan implementation by selecting 1 of 7 categories: thoughts, emotions, motivation, situation, self-belief, financial, and social. Participants are prompted to describe the selected barrier in an open text field and to detail how that barrier can get in the way of their action plan. The app then prompts participants to identify what they can do right now to overcome the barrier and get back on track with the plan (open text field).

Once the plan is saved, commitment and self-efficacy activities facilitate the strategy’s engagement and throughput. This activity involves focusing on character strength and mental rehearsal [70,71]. Consideration of character strengths is prompted by *Name your strength that can help you stick to your plan and overcome the barrier you have identified. Write down exactly how this strength will be useful* (open text field). To undertake mental rehearsal, the person is prompted to imagine implementing their plans. A prompt for mental imagery is provided as follows:

You have decided what to do, so take a moment to visualize yourself doing it. Close your eyes and imagine yourself doing what you need to do. Imagine it going well. Imagine feeling happy that you take this action. You feel proud of yourself and feel good because you have control. You are ready to do this action right now.

Once completed, the app provides an encouraging message:

Great work in putting together your plan and identifying your strengths. This is really going to help you stick to your gambling goals. We will check in again in a few hours to see how you are going.

#### Control Condition—Strategy Group Names Only

Participants allocated to the control condition will receive a list of all 25 strategy groups (names only), with no specific strategies or implementation guidance provided. Once participants select a strategy group name, such as *Talk to someon*e, the app provides an encouraging message: *It is a great idea to* (insert strategy group name)*. We will get in touch with you soon to check how you are doing*. Providing information at the strategy group level is similar to responsible gambling messaging and reflects a real-world experience of these messages.

### Consumer Participation

People with lived experience of gambling problems are represented in all aspects of *Gambling Habit Hacker*, including identification of intervention content, testing of app functionality, and recommendations for future improvements via postintervention survey items and semistructured interviews. The app includes detailed implementation support, delivering >70,000 words of content. This content was sourced from consumer accounts representing >2000 individuals from various sources, including counseling transcripts [26], in-venue surveys [23], online forums [17], and community-based quantitative and qualitative surveys [15,30]. Within the app, quotes are taken directly from this lived experience research, selected to align with each strategy group.

### Within-Group Evaluation

In addition to MRT, this study will include a within-group follow-up evaluation over a 6-month period to (1) examine within-group change over the 6 months following the end of the MRT and (2) identify predictors of these longer-term treatment outcomes (including usage of the app over the follow-up period). Surveys taking 10 to 15 minutes will be administered before intervention (via the app), as well as after intervention and at the 6-month follow-up (via Qualtrics). Descriptive and covariate measures will include sociodemographic characteristics (age, sex, current residence, primary ethnicity, and personal annual gross income), problem gambling activities (6 types of gambling), and intended gambling behavior as measured by the TimeLine Follow-Forward [58], volitional phase [72], and help seeking [73]. To assess the volitional phase, participants will be presented with 4 statements: I am deciding whether I need to change my gambling (predecisional); I am getting ready to change my gambling (postdecisional); I have already started to change my gambling (actional); and I have successfully changed my gambling and want to maintain this change (postactional). Posttrial and 6-month follow-up participants will be asked to report on their previous help-seeking behavior using 9 items from the Help-Seeking Questionnaire [73]. This includes 5 items related to high-intensity help seeking and 3 items related to low-intensity help seeking. An item related to self-directed help seeking will also be administered to assess engagement with self-exclusion.

The primary outcome for the within-group evaluation will be gambling expenditure (measured using a TimeLine Follow-Back at the preintervention evaluation, the EMA data collected during the intervention period and amalgamated for the posttreatment evaluation, and single items at the 6-month evaluation). Secondary outcomes will include gambling symptom severity measured using the G-SAS [57], gambling frequency with the TimeLine Follow-Back at the preintervention evaluation (EMA data at the posttreatment evaluation and single items at the 6-month evaluation) [74], psychological distress measured using the Kessler 6 Psychological Distress Scale [75], personal well-being measured using the Personal Wellbeing Index [76], the Brief Situational Confidence Questionnaire [77], and planning propensity measured using an adapted action control questionnaire that assesses action planning, coping planning, and action control [78]. A summary of the measures and the measurement time points (before intervention, after intervention, and follow-up) for the within-group evaluation are presented in Multimedia Appendix 2.

To enhance engagement with the posttreatment and 6-month follow-up evaluations, the following protocols will be implemented. An email will be sent to all participants to prompt survey completion, with a second reminder email for those who fail to complete within a week. An advance notice email will also be sent a week before the 6-month surveys are administered. For those who have not completed the survey after a further week, up to two reminder telephone calls will be made by a clinical or qualitatively trained researcher. At each time point, the option to complete the survey over the phone with a trained research fellow will be offered. Participants who do not complete posttreatment evaluation will be contacted at the 6-month evaluation unless they have withdrawn from the study.

During the 6-month evaluation period, *Gambling Habit Hacker* will be available to participants for continued use. The tailored intervention content will be available on demand, meaning that participants can complete EMAs at any time of the day or night. The intervention content will still be tailored, but participants will not receive the 3 times daily prompts for EMA completion. This approach is designed to encourage participants to incorporate action- and coping planning skills in everyday situations and settings when there is a shift in motivation, self-efficacy, or the presence of high-risk situations.

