## Methods

### Trial Design

A 28-day MRT will be used to facilitate the optimization of *Gambling Habit Hacker*. In this trial, *decision points* comprise notifications that participants will receive via their smartphones to complete a time-based EMA 3 times a day. In each EMA, *tailoring variables*, including strength of intention, goal self-efficacy, urge self-efficacy, and high-risk situations, are used to determine intervention eligibility according to *decision rules* based on EMA cutoff points. At each decision point, participants will be randomly allocated to either the intervention or a control condition (*intervention options*). This MRT will evaluate the JITAI entirely as a *push* intervention.

This MRT will be supplemented with (1) a 6-month within-group follow-up that explores the long-term impact of the app on gambling expenditure (primary distal outcome) and a range of secondary outcomes (gambling frequency, gambling symptom severity, psychological distress, well-being, situational confidence, and planning propensity) as well as the predictors of longer-term treatment outcomes and (2) an evaluation of the acceptability of the JITAI via postintervention surveys, app use and engagement indices, and semistructured interviews.

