### Distal and Proximal Outcomes

The *distal outcome* for *Gambling Habit Hacker* is gambling expenditure. The *primary proximal outcome* is goal adherence (operationalized as a binary outcome, with success defined as actual gambling expenditure being no greater than 10% higher than planned gambling expenditure). In exploratory analyses, the impact of altering the flexibility percentage (eg, 20% flexibility) and continuously scaled measures of adherence may also be explored. To specify expenditure goals over the 28-day MRT, participants are required to indicate their intended gambling episodes and associated expenditure during preintervention measurement using a TimeLine Follow-Forward [58]. Actual expenditure will be collated via the event record in each EMA: S*ince the last time you checked in, how much have you spent in $ gambling? Record 0 if you have not gambled*. *Secondary proximal outcomes* are drawn from EMA data, which allows us to examine changes across the course of the intervention. Outcomes include the strength of intention to adhere to gambling goals, goal self-efficacy, and urge self-efficacy, all of which are measured in the subsequent EMA (see the *Tailoring Variables* section for information on the source and description of each variable).

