### Statistical Analyses

To assess the research questions, the method of generalized estimating equations will be used, with an appropriate link function for the outcome of interest (eg, logit or identity). Although an exchangeable working correlational structure is intended to be used for the analyses, considerations will be given to alternative correlational structures based on the observed within-person correlation pattern over the course of the study (eg, independent or auto-regressive). For all MRT analyses, the (lagged) outcome of interest (eg, adherence to expenditure limit at Time_t+1_) will be regressed on a variable denoting the treatment received (ie, intervention vs control) at Time_t_, as well as covariates (including unbalanced time). The primary analyses will explore the effect of intervention versus control on the probability of adherence to expenditure limits in the subsequent episode. The identification of the conditions under which the interventions are most beneficial and how the effect of the interventions changes over the course of the MRT will be examined by specifying interaction terms between the intervention variable and interaction variables of interest (eg, strength of intention and time).

The long-term outcomes of the intervention (within-group follow-up evaluation) will be explored, whereby distal outcomes will be assessed using generalized estimating equations by regressing the outcome of interest (eg, gambling expenditure) on a variable denoting time (ie, before intervention, after intervention, and 6-month follow-up) and covariates. The identification of factors predicting longer-term outcomes will also be assessed by regressing the outcome of interest (eg, clinically significant changes in gambling expenditure) with selected preintervention, postintervention, and app usage variables. Where appropriate, missingness will be addressed using multiple imputations with appropriate accounting for the multilevel nature of the data (eg, multilevel multiple imputation).

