Quantitative evaluation indicated that all scores were higher than the minimum acceptability score of 3, which suggests that the app may be helpful [85] (Multimedia Appendix 3). Intervention content was rated highly in terms of strategy relevance to plan creation (>7 out of 10), helpfulness of strategy description (almost 8 out of 10), and quotes on lived experience were perceived as helpful (>7 out of 10). Experts rated planning functionality highly (>7 out of 10) and indicated slightly lower scores for helpfulness of information in coping planning (>6 out of 10). The lowest rated items were TimeLine Follow-Back (calendar to assess past-month gambling behavior) and TimeLine Follow-Forward (calendar to assess planned gambling behavior over the next month), where ease of completion was rated as just over 3 out of 10. Qualitative data were generally positive in terms of comprehensiveness and quality of information, credibility, graphics, and interactivity. The main issues raised were related to functionality in terms of loading times, errors in the notification schedule, and difficulty in entering and saving data in the timeline calendars. The evaluation also indicated that the participant burden needed to be reduced in terms of the length of pretrial measures and the time required to complete the EMA items. Technical issues, including user acceptability concerns, were addressed through extensive redevelopment of the calendars, reducing the number of items in the baseline and EMAs, and correcting the schedule of notifications. A total of 3 testers subsequently used the app again and confirmed that the issues had been satisfactorily resolved.

The user testing phase of the app-administered action planning and coping planning as separate interventions, where coping planning was delivered 30 minutes after action planning and only where participants indicated that they had not implemented their action plan. User testing revealed that this was confusing and was an added burden, which meant most participants did not complete coping plans even if they were assessed as eligible (ie, they had not implemented the action plan). In response to this finding, we merged action- and coping planning as a single intervention delivered concurrently (without a time delay).

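### Gambling expenditure, the primary distal outcome, is measured by a different method at each time point, so its change over time mixes a change of method with a change in gambling

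*Protocol article*

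**What the plan says.** The Within-Group Evaluation section of the protocol article states: "The primary outcome for the within-group evaluation will be gambling expenditure". It then names one method per time point. Before the intervention, expenditure is "measured using a TimeLine Follow-Back at the preintervention evaluation". Afterwards it comes from "the EMA data collected during the intervention period and amalgamated for the posttreatment evaluation, and single items at the 6-month evaluation". Gambling frequency, a secondary outcome, gets the same three methods. The user-testing part of the Results describes the baseline method as a past-month calendar. The same Within-Group Evaluation section moves the surveys from the app at baseline to Qualtrics afterwards.

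Under Statistical Analyses, the distal outcome is regressed by generalized estimating equations (GEE) "on a variable denoting time (ie, before intervention, after intervention, and 6-month follow-up) and covariates". That section also applies Reliable Change Indices to all primary and secondary outcomes. It classes clinically significant change by functional score ranges where these exist, and otherwise by an improvement of at least 25%. Trial Design makes this a within-group follow-up, so there is no comparator.

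**The concern.** A time coefficient can be read as change in gambling only if the same behaviour would give the same figure at each time point. Here the method changes whenever time changes. A calendar covering the past month, a running sum of short-interval reports and summary items are different recall tasks, and nothing in the article shows that they give equal totals.

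Two contrasts are affected. One is baseline to 6 months, which carries the long-term claim. The other is posttreatment to 6 months, which is the first stated aim of the within-group evaluation. With no comparison group, a method shift cannot cancel. At stake is the statement in the Discussion that this evaluation will establish whether expenditure falls, and with it the recovered, improved, unchanged and deteriorated classes for expenditure and frequency.

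**Working it through.** **1. Methods against time points (expenditure and frequency)**

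| Time point | Method |
|---|---|
| Before intervention | TimeLine Follow-Back, past-month calendar |
| After intervention | EMA records, summed |
| 6 months | Single items |

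There are three time points and three methods, one each. Write the mean at time *t* as behaviour(*t*) + shift(method at *t*). The coefficient for 6 months against baseline is then [behaviour(6 months) − behaviour(baseline)] + [shift(single items) − shift(calendar)]. The second bracket can be estimated only if two methods are used at the same time point, and the text describes no such overlap. Covariates, the choice of working correlation and multiple imputation do not supply it.

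**2. The plan's own figure.** Sample Size gives 200 recruited with 40% attrition: 200 × (1 − 0.40) = 120 at 6 months. This reproduces. The article gives no SD, effect size or calibration between methods for the distal outcome, so steps 3 to 5 rest on assumptions.

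**3. Apparent change.** Suppose the single items record a fraction *k* of what the calendar would, and the true relative change is *t*. The apparent change is *k*(1 + *t*) − 1.

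| *k* | No true change | True fall of 20% |
|---|---|---|
| 0.75 | −25% | −40% |
| 0.8 | −20% | −36% |
| 0.9 | −10% | −28% |
| 1.0 | 0% | −20% |
| 1.25 | +25% | 0% |

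The error can go either way: it can create a fall or hide one.

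**4. Chance of a false significant change.** Assumptions: *n* = 120, no true change, SD of the within-person log change 0.8, 1.0 or 1.3, two-sided 5% test, zero spending ignored. The standardized shift is ln(*k*) / (SD/√120). For *k* = 0.9 and SD = 0.8, SE = 0.8/√120 = 0.0730 and ln 0.9 = −0.1054. The shift is −1.44 and the rejection probability is 0.30.

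| *k* | SD 0.8 | SD 1.0 | SD 1.3 |
|---|---|---|---|
| 0.9 (false fall) | 30% | 21% | 14% |
| 0.8 (false fall) | 86% | 69% | 47% |
| 1.25 (false rise) | 86% | 69% | 47% |

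A version without the log scale agrees. Method shifts of 0, 0.1, 0.2 and 0.3 SD of the change score give rejection rates of 5%, 19.5%, 59% and 91%.

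**5. The 25% rule.** With no true change, the share classed as improved by at least 25% is Φ((ln 0.75 − ln *k*)/SD).

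| SD | *k* = 1 | *k* = 0.8 | Increase |
|---|---|---|---|
| 0.8 | 36% | 47% | 11 points |
| 1.0 | 39% | 47% | 9 points |
| 1.3 | 41% | 48% | 7 points |

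Increases are computed before rounding. Most of the false improvers are there already at *k* = 1, from ordinary variation. The method shift adds 7 to 11 points.

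**The case against.** The primary objective is the randomized proximal effect. Both conditions use the same EMA expenditure item, so that comparison is untouched. The 6-month part supplements it and is mostly described as exploratory. It has no comparator, other help seeking is allowed and the app stays available, so even identical instruments would not show that the app caused a change. Symptom severity, distress, well-being, situational confidence and planning each name one instrument, so the long-term picture does not rest on expenditure alone. All of this stands and limits the severity. It does not remove the point, because expenditure is the named primary distal outcome and the Discussion promises a finding on it.

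A reader might infer that the single items under-report and that any fall seen at 6 months would be an artefact. The documents do not support this. They give no wording or recall window for the single items and no evidence on the direction of a shift. The figures above show sensitivity and are not a prediction. The log scale also cannot handle zero spending, although abstinence is an allowed goal.

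Multimedia Appendix 2, which lists measures by time point, is not shown, so a common item cannot be excluded with certainty. The article's text is nevertheless explicit about the method at each time point and mentions no overlap.

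Burden is a fair consideration too. Testers rated the ease of completing the timeline calendars at just over 3 out of 10 and asked for shorter assessments. That favours short items as the common measure, but it is no reason to have none.

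**Conclusion.** The point holds for the distal evaluation. For expenditure and frequency, time and method are completely aliased, in both the baseline-to-6-month and the posttreatment-to-6-month contrasts, and the individual change classes carry the same fault. This is a stated design choice. A later analysis plan cannot repair it unless a common measure is collected.

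The size is unknown. Under the stated assumptions, a 10% under-reading gives a false significant fall in 14% to 30% of trials and a 20% under-reading in 47% to 86%. An over-reading of 25% would produce a false rise as often, or cancel a true 20% fall. It would go too far to conclude that the trial's main result is compromised, since the randomized comparison is unaffected. The point is important for the distal claim and is not a must-fix for the primary objective.

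**What to change.** Collect one common measure of expenditure and of frequency, with the same recall window, at baseline, posttreatment and 6 months. The simplest way is to add the 6-month single items to the preintervention and posttreatment surveys. Base the distal contrasts and the change classes on that measure, and keep the calendar and EMA totals as supporting measures. Repeating the calendar for everyone would also give like-for-like data, but at a higher burden.

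Participants enrolled without the baseline items (36 had been recruited by 26 May 2022) should complete the calendar at 6 months together with the single items. Analyse their calendar-to-calendar change as a separate stratum or as a sensitivity analysis. Do not pool it with item-to-item change without an instrument term. There is time for this: advertising began on 11 April 2022, and 28 days plus 6 months from then is about 9 November 2022.

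The cost is about one minute of extra survey time, a minor amendment, a sentence in the analysis section and a 6-month calendar for the early enrolees. That calendar must be built in Qualtrics or completed in the app. The move from app to Qualtrics remains as a change of mode and should be stated as a limitation.
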